### Secondary outcomes

Secondary clinical time-to-event outcomes (progression of caries; tooth restoration failure and re-restoration) will be analysed in a similar manner to the primary outcome. Pulp exposure will be analysed using logistic regression adjusted for minimisation covariates and a random effect for clinician included. Secondary outcomes reported by participants will be analysed using mixed effects generalised linear models (using the appropriate link function for the outcome distribution) for repeated measures. Models will make use of data available at all time points, adjusted for minimisation covariates, fixed effects for treatment and (nominal) time points, and random effects for participant and clinician. The primary time point of interest will be three years post-randomisation. Treatment effects will be estimated using a treatment-by-time interaction and presented with 95% confidence intervals.

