#### Identifying and recruiting participants

The trial will aim to recruit 65 practices (each recruiting an average of 10 participants) to achieve the target of 623 participants. Trial clinicians will identify patients at routine visits that meet the inclusion criteria and explain the trial. Eligible patients who express interest will be given a participant information leaflet (Additional file 1) and an appointment for their treatment as per current clinical practice. At the treatment visit the patient will be given the opportunity to clarify any questions prior to informed consent being obtained and recorded on a written consent form (Additional file 2).

The eligibility of all participants will be assessed and determined by their dental practitioner following clinical and radiographic examination according to pre-determined criteria. Those who do not wish to take part will receive caries removal and restoration as per current practice. Those who are eligible and wish to take part will give informed consent to the clinician providing treatment.

A baseline questionnaire will be completed by the participant to collect baseline patient centered outcomes. Randomisation will then take place using an online randomisation system. If the participant has more than one eligible tooth, a trial tooth will be selected at random by the randomisation application. The randomisation algorithm will use recruitment site, number of eligible teeth (1; > 1) and type of caries (primary and secondary) as minimisation covariates to allocate to treatment intervention and control groups in a ratio of 1:1To maintain participant blinding, participants will not be informed of their allocated treatment group following randomisation. Baseline clinical information will be recorded by the clinician after the treatment has been provided.

After the initial intervention participants will receive any treatment deemed clinically appropriate by their dentist as per normal practice.

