### Participant reported outcomes

Patient focused outcomes will be recorded pre-randomisation at the baseline visit and on an annual postal or online follow-up questionnaire until 3-years post-randomisation (except when indicated otherwise).

Dental pain and need for dental pain relief will be recorded on the annual patient questionnaire. Dental pain will be measured using a Numerical Pain Rating Scale (NPRS) [24]. Health status will be assessed using the generic EQ-5D-5L, consisting of five dimensions of Health-Related Quality of Life (HRQoL) [25]. Oral Health Related Quality of Life will be assessed using the Oral Health Impact Profile 14 (OHIP-14). OHIP-14 is the most commonly used validated oral HRQoL measure and has been used successfully in previous HTA trials [26]. Oral Health behaviours will be assessed at baseline and 3-years post-randomisation using questions about type of toothbrush, brushing twice a day for 2 min, frequency of interdental cleaning and behaviour after brushing.

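### The stated model for participant-reported outcomes neither adjusts for the baseline score nor sets a common baseline mean, so year-3 EQ-5D-5L and OHIP-14 estimates are less precise than the data allow

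*Protocol article*

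**What the plan says.** Under Analysis plan, Secondary outcomes, the Protocol article gives the model family: "Secondary outcomes reported by participants will be analysed using mixed effects generalised linear models". It adds that "Models will make use of data available at all time points" and lists the terms: "adjusted for minimisation covariates, fixed effects for treatment and (nominal) time points, and random effects for participant and clinician". The effect measure is also fixed: "Treatment effects will be estimated using a treatment-by-time interaction and presented with 95% confidence intervals". The visit that matters is named: "The primary time point of interest will be three years post-randomisation".

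The minimisation covariates are defined under Identifying and recruiting participants: "The randomisation algorithm will use recruitment site, number of eligible teeth (1; > 1) and type of caries (primary and secondary) as minimisation covariates". None of them is a patient-reported score.

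On timing, the section Participant reported outcomes says: "Patient focused outcomes will be recorded pre-randomisation at the baseline visit". Annual questionnaires follow up to three years. Table 1 schedules EQ-5D-5L and OHIP-14 at baseline, on the annual questionnaire and at 36 months. Patient satisfaction has no baseline entry. The article does not say whether baseline is one of the time points in the model.

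**The concern.** For a quality-of-life scale, the participant's own score before treatment is usually a strong predictor of the later score. Here it is collected for every participant asked to complete the baseline questionnaire. The listed terms give it no place as a covariate, and it does not enter through the minimisation factors.

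If baseline instead enters as a response, a treatment main effect together with a treatment-by-time interaction leaves the two baseline means free to differ. The interaction at year 3 then compares changes from baseline, which is not equivalent to adjusting for baseline.

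At stake is the width of the intervals for the year-3 EQ-5D-5L and OHIP-14 effects. The sample size section already allows for 30% attrition by the end of year three, so precision on these outcomes should not be given away. Because the time points are undefined, the interaction coefficient is also ambiguous. With baseline as reference it is a difference in change. With year 1 as reference it is the year-3 effect minus the year-1 effect, which is not the year-3 effect.

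**Working it through.** The article states no power or precision figure for participant-reported outcomes, so there is no figure of its own to reproduce. The check compares the variance of the year-3 effect under the possible models.

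**Inputs from the Protocol article.** The model terms and effect measure come from Secondary outcomes under the Analysis plan, the baseline schedule from Participant reported outcomes and Table 1. The sample size section gives 623 participants and 30% attrition at year three.

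**Assumptions.** The correlation r between baseline and year-3 scores is not given, so 0.3, 0.5 and 0.7 are shown. The model is linear, with equal variance at each visit, the same correlation between any two visits, complete visits and equal arms.

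**Formulas**, with the variance of the year-3 arm difference from follow-up scores only set to 1:

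- Follow-up only, no baseline term: 1.
- Baseline as a response with a free treatment main effect, year-3 interaction: the change score has variance 1 + 1 − 2r, so the factor is 2(1 − r). The year-3 arm difference from this same model (main effect plus interaction) stays at 1.
- Baseline as covariate, or as a response with a common mean: 1 − r².

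Change contrast against adjustment: 2(1 − r)/(1 − r²) = 2/(1 + r), which exceeds 1 for every r below 1. It is 1.54, 1.33 and 1.18 at r = 0.3, 0.5 and 0.7. Follow-up only against adjustment: 1/(1 − r²), which exceeds 1 for every non-zero r.

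| Assumed r | Follow-up only | Change contrast | Adjusted | Interval narrower than follow-up only | Interval narrower than change contrast |
|---|---|---|---|---|---|
| 0.3 | 1.00 | 1.40 | 0.91 | 1 − √0.91 = 5% | 1 − √(0.91/1.40) = 19% |
| 0.5 | 1.00 | 1.00 | 0.75 | 1 − √0.75 = 13% | 1 − √(0.75/1.00) = 13% |
| 0.7 | 1.00 | 0.60 | 0.51 | 1 − √0.51 = 29% | 1 − √(0.51/0.60) = 8% |

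A generalised least squares calculation with one baseline and three follow-up visits under this correlation gives the same factors.

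**In outcome units.** Suppose the 30% attrition applies to the questionnaires, so that 623 × 0.7 ≈ 436 are analysed. Borrow 90% power and two-sided 5% from the primary outcome as a yardstick. The detectable difference is (1.96 + 1.28) × √(4v/436) SD, where v is the relative variance:

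- Follow-up only: 0.31 SD.
- Change contrast: 0.37, 0.31 and 0.24 SD at r = 0.3, 0.5 and 0.7.
- Adjusted: 0.30, 0.27 and 0.22 SD.

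At r = 0.5, 1/0.75 = 1.33, so adjustment is worth about one third more respondents than a follow-up-only analysis.

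**The case against.** The strongest reply is that the baseline may well be used. A reader might infer from the covariate list that the pre-randomisation score is discarded. The article does not support that. It promises to use data from all time points, and a model with nominal time, a participant random effect and a treatment-by-time interaction is a standard way to carry baseline as a response. This reply stands against the claim that baseline is ignored. It does not remove the precision loss, because without a common baseline mean the interaction is still a change contrast.

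Second, Proposed analyses leaves full specification to a statistical analysis plan that is not shown, and the article is condensed. A bare omission would therefore be no point. Here, however, the article states the terms and the effect contrast. An analysis plan that follows them literally inherits the loss, and one that adds the baseline score or the constraint goes beyond the published list. It may already do so.

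Third, a reader might infer bias from chance baseline imbalance. Randomisation keeps both estimates valid, and the follow-up-only interval already allows for chance imbalance. The matter is efficiency.

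Fourth, the size is assumed. At r = 0.3 the gain over follow-up only is about 5% of interval width. At r = 0.7 the gain over the change contrast is about 8%. The planned models are generalised linear, with a link chosen for the outcome's distribution, so the factors need not carry over exactly to skewed or bounded scores. This stands.

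Finally, the point does not reach every participant-reported outcome. Patient satisfaction has no baseline entry in Table 1, and the text places dental pain on the annual questionnaire.

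**Conclusion.** The point holds as one of efficiency and clarity for secondary outcomes that have a baseline value, chiefly EQ-5D-5L and OHIP-14. On either reading of the time points, the model as written gives a less precise year-3 estimate than the collected data allow.

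With r between 0.3 and 0.7, the interval under adjustment would be 5% to 29% narrower than with follow-up scores only, or 19% to 8% narrower than with the change contrast. These figures rest on an assumed r and on a linear model with equal variances and complete visits. The documents do not support a claim that the baseline is certainly left out, that the estimates are biased, or that all participant-reported outcomes are affected. The primary outcome and its sample size are not touched.

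**What to change.** State how the baseline score enters, in the article's terms or in the analysis plan, for EQ-5D-5L, OHIP-14 and any other outcome with a baseline value. Either of two forms will do:

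- Define the modelled time points as years 1 to 3 (or the follow-up visits at which that outcome is collected), and add the baseline score and its interaction with time as fixed covariates.
- Keep baseline as a response, but give both arms a common baseline mean.

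In both cases, name the year-3 treatment contrast as the reported effect, so that it does not depend on which time point is the reference. Leave the model unchanged for outcomes without a baseline value, such as patient satisfaction.

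The cost is a sentence or two and no new data. It can be settled before the single final analysis. The only downside is that a few missing baseline scores need simple handling under the covariate form, for example mean imputation.

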### Planned subgroup analysis

Subgroup analyses on the primary outcome will explore the possible modification of treatment effect by age and number of lesions. This will be done by including treatment-by-factor interactions in the model and they will be classified as exploratory analyses.

### Proposed frequency of analysis

From the internal pilot phase we will report estimates of recruitment rates and potentially eligible participants, together with appropriate confidence intervals. There are no planned interim analyses of the primary or secondary outcomes; one final analysis will occur at the end of follow-up.

### Missing data

Strategies with proven effectiveness in improving retention will be used to minimise missing data [36]. For participants who do not return or are censored early in the trial, dental practices will be contacted to find out potential reasons for missing data if they are available.

Participants with no event will be censored at their last visit with sustained tooth vitality. It is anticipated that a small proportion of participants will not return at all, and a further proportion will be censored early in the trial because they do not come back to their clinician. The team will consider how robust the findings are to these missing data using multiple imputation approaches under an assumption of missing at random, and using pattern mixture models if appropriate. In participants with more than one eligible tooth, we will repeat our primary analysis with a clustering effect for participant.

Routinely collected data will be considered to supplement missing outcome data if deemed appropriate. We will undertake a validation analysis comparing (primary outcome) CRF data with routinely collected tooth-level data which will also provide the opportunity for secondary and economic outcome data analysis if the data are valid. This will be detailed in a data linkage analysis plan.

### Transfer of data

Data transfer will adhere to the processes detailed in the CHaRT Standard Operating Procedure book.

The data will be de-identified before it is securely transferred. The data will be transferred using ZendTo. This is a secure web-based service which can be used to securely transfer data between colleagues both inside and outside the university. Files are stored on and accessed from the University’s secure server, and all files are checked for viruses when they are uploaded. The de-identified data will be encrypted before it is sent with ZendTo, using Office365 AES-256 encryption.

However, sometimes it may be necessary to transfer files on CD or USB stick. In such cases, a robust system logging the receipt of sent items must be in place either for a CD coming into the centre or leaving the centre—for example, by registered mail or courier, requiring signature on delivery. As with electronic data, the data on the CD/USB stick should be encrypted and password protected using an acceptable standard of encryption currently available (at least 256-bit encryption).

Data transferred from CHaRT to external parties will be subject to approval by the Project Management Group using a data request form.

Access to data linked to NHS Scotland routine administrative data for outcome analysis will be undertaken within the NHS Scotland National Safe Haven infrastructure [37].

## Economic evaluation

A full economic evaluation will be conducted. This will include a trial-based analysis at three years follow-up and a decision model to assess economic value over an extrapolated lifetime horizon. The primary economic outcome will be net benefit, WTP minus cost (NHS and patient perspective) evaluated in a cost–benefit analysis (CBA) framework, modelled over a lifetime horizon. CBA is chosen as the preferred framework because of concerns that generic QALY measures are not sufficiently sensitive to capture the value of important outcomes in dental care. Cost Utility Analysis (CUA) reporting cost per QALY will also be conducted as a secondary economic analysis to comply with NICE guidelines for technology appraisal.

### Estimation of costs

Routinely collected dental claims data will be used to assess the costs to the NHS, and co-charges to patients of NHS provided dental treatments. Routine datasets will be supplemented with data collected using CRFs in the dental practice at each visit. Remaining resource use data, NHS and patient perspective costs directly related to dental problems will be collected using patient questionnaires. NHS costs of providing SCR and CCR will be based on the appropriate NHS contract-based payments to clinicians in the respective UK regions for the base case analysis. Contract payments detail the cost burden to the NHS but may not capture the full opportunity cost of time spent and materials used to deliver the interventions. Therefore, a micro-costing approach will also be used as a secondary analysis. Resource use data for the intervention micro-costing will include staff resource use and time, and consumables with information collected in a detailed CRF at the point of intervention delivery. Patient perspective costs will include patient co-charges for NHS treatments, time and travel costs, time-off work, privately purchased care and self-purchased dental care products. The participant time and travel cost questionnaire will be sent to a random sample (N = 347) of trial participants. The required sample reflects the minimum number of respondents contributing complete data that is required to enable a multi-variable regression to estimate costs according to a range of predictor characteristics of the sample. The minimum sample size is calculated from the formula N ≥ 50 + 8(k) [38] where k is the number of independent categories of the model assuming linear additive effects and no interactions. For k = 15 explanatory variables in the model, the minimum number of fully complete responses to the questionnaire is N ≥ 50 + 8(15) ≥ 170. Assuming a questionnaire non-response rate of 30% and a further item non-response rate that would preclude running the model of 30% of returned questionnaires (as per the IQuaD study), the minimum number of questionnaires that need to be sent to obtain the required sample is N = 347 (170/0.7/0.7). The questionnaire will be administered to a random sample of respondents split across the one and two-year annual follow-up time-points. The information collected will also be used to validate an external prediction model of time and travel costs that can be used in future research. Incremental NHS and patient perspective costs for SCR vs CCR will be estimated using generalised linear regression models with appropriate specification of distributions for cost and outcomes data and adjustment for baseline covariates.

### Estimation of benefits

Willingness to pay (WTP) for the cost–benefit analysis (CBA) will be elicited from a discrete choice experiment (DCE). The DCE will be conducted with a nationally representative sample of the UK general population, using online panel surveys. The DCE will explicitly value preferences for provision of SCR and CCR, together with a range of plausible outcomes from the trial (e.g. sustained tooth vitality, longer term risk of repeat treatments and tooth loss). The DCE will examine the trade-offs between the potential benefits and risks of different treatment strategies. A cost attribute will be included to enable calculation of WTP. The DCE will also be used to assess the acceptability of SCR and CCR and predict uptake according to patient characteristics (investigating issues of preference heterogeneity for treatment). The target sample size for the DCE (N = 1067) is calculated using Dillman, 2007 [39], using an estimate of the population of interest (i.e. the UK general adult population) =  ~ 52 million), a conservative estimate of variation in the answers for the question of interest of 0.5, and an assumed margin of error of 3% in line with public opinion research, with a confidence level of 95%. A further sample of 100 respondents will be sought for a pilot study of the DCE. As a secondary objective, we will measure benefits in terms of QALYs gained, based on patient responses to the generic EQ-5D-5L health related quality of life measure.

### Trial based economic evaluation

Economic evaluations typically take the form of cost-utility (i.e. cost per QALY). However, in the context of dentistry, there are concerns that generic EQ-5D based QALYs lack the sensitivity to capture the processes and outcomes of care that are of value to patients and decision makers. Different perspectives of benefits will therefore be evaluated (Willingness to pay (WTP) for the interventions and outcomes, WTP for dental health outcomes only, and Quality Adjusted Life Years (QALYs). Costs will be evaluated from an NHS dental, all NHS, and participant perspective. Costs and benefits will be combined to estimate incremental net benefit (WTP minus costs), incremental net dental health benefit, and incremental cost per QALY gained for SCR vs, CCR over the three year trial follow up period. Deterministic sensitivity analyses will be undertaken to test the impact of assumptions and analysis methods on results. Subgroup analysis will be conducted at the region level if data allow in order to explore the potential impact of different payment systems across the UK regions on results. Results will be plotted on the cost–benefit and cost-effectiveness planes to illustrate the impact of sampling uncertainty on results.

### Decision modelling

The trial results will be extrapolated over a lifetime horizon using a de novo tooth-level Markov model. The model will be built as a cohort model, but we will retain the option to move to a more flexible micro-simulation model if appropriate. Results will be reported using the same net benefit framework as the within trial analysis. The final model structure and health state definition (e.g. loss of tooth vitality, tooth-restoration-complex failure, caries progression, and tooth loss) will be developed in conjunction with dental and patient experts. Survival analysis methodology will be used to assess the time to transition between health states, with survival curves fitted over an extended time frame (patient’s life time) to extrapolate the time to event data from the trial. The survival analysis will be supplemented with data from cohort studies and literature reviews to complete population of model transition probabilities and relative effects as required. Cost data (NHS and patient perspective) for health states will be sourced from the trial data and routine data sources (PHS / BSA). Benefits in terms of WTP will be sourced directly from the DCE for specific health states (e.g. WTP to avoid loss of tooth vitality, tooth-restoration-complex failure, caries progression or tooth loss), together with WTP tariffs from previously conducted DCE studies [40]. Sensitivity analyses will explore the impact of key assumptions on results. Gaps in the evidence base will be identified and their potential impact on efficiency (net benefit) explored through sensitivity analysis. Results will be reported according to the same cost and benefit perspectives as detailed for the trial-based analysis. Findings will be illustrated using cost-effectiveness and cost–benefit acceptability curves. A value of information analysis will be undertaken to determine the need for future research to resolve any residual decision uncertainty and an expected value of partial perfect information (EVPPI) analysis will be used to prioritise future cost-effectiveness research objectives.

